### Interventions

#### Overview

MBRP has been tested in randomized clinical trials as a “stand-alone” treatment (without prior treatment) [61], as a primary treatment following detoxification and stabilization [45], as a “rolling group” component of residential treatment [62], and as an “aftercare” intervention following community treatment as usual [44,46]. This study is the first randomized trial of MBRP compared to referral to mutual support in the community and the first trial of MBRP as a continuing care intervention whereby individuals can attend as many sessions as they want (ie, “rolling group”). MBRP is especially well-suited for adaptation from a discrete treatment episode to continuing care, given its emphasis on establishing and maintaining a mindfulness practice that can flexibly be applied in any situation. This contrasts with other evidence-based treatments that emphasize teaching clients to use learned skills for specific high-risk situations (eg, cognitive behavioral therapy–based relapse prevention plans).

Given the focus on MBRP as a continuing care intervention, it was important to select a comparator that reflected existing continuing care models. Continuing care for AUD is largely based on referral to mutual support groups; therefore, referral to mutual support groups was selected as the comparator [63]. We chose a 2-group design and did not randomize to different kinds of mutual support (eg, SMART Recovery vs AA), such that client participants received referral to multiple mutual support options and were informed that they were welcome to select and try out any that interested them (eg, SMART Recovery and AA). Thus, this study assesses the effectiveness of MBRP as continuing care as compared with the typical approach of referring individuals to mutual help, regardless of which mutual help groups participants attend.

Interventions are not modified or discontinued by the research team for any reason, although trial participants could opt to discontinue attending the intervention conditions at any time. No concomitant care or additional interventions are prohibited during the trial.

Mutual support groups are freely delivered in the community and will continue throughout the trial. MBRP groups are offered throughout the duration of the study, as long as there is interest by at least 2 or more group members. If groups are not continued due to low census, and any one individual is interested in continuing to practice mindfulness, the research team will refer MBRP client participants to local (if available) or online Recovery Dharma groups, which will offer the opportunity for ongoing mindfulness practice related to recovery.

#### Orientation Session

For both intervention conditions, the first session is an individual orientation delivered via Zoom by a study team member. Orientation session leaders include the research coordinator, study coinvestigators, a postdoctoral fellow, and clinical psychology graduate students. This orientation session is approximately 30 minutes and includes brief motivational interviewing [64], an overview of the project timeline, an introduction to the assigned intervention condition, and instructions for collecting blood samples via a mailed dried blood spot card.

#### MBRP Condition

In addition to the elements described above, the orientation session for the MBRP condition includes a review of the Zoom environment, an opportunity to learn Zoom for group sessions (eg, applying virtual backgrounds, breakout rooms, video and mute functions, swapping speaker, and panel view); an overview of MBRP; and an introduction to a free, MBRP mobile app created specifically for this study.

MBRP is delivered by trained facilitators and uses an existing rolling group treatment manual that has demonstrated effectiveness [62] and has been used feasibly via Zoom since March 2020. Participant worksheets and home practices were adapted from the closed-format MBRP manual [49] and guided meditations were drawn from the PracticeMBRP and MindfulRP websites. The rolling group manual consists of 8 sessions of 60 minutes each, covering the content described in Table 1.

Each session begins with a brief mindfulness practice and a discussion of mindfulness concepts (eg, “what is mindfulness?”) and the role mindfulness may play in recovery. The discussion encourages participants to apply the practices learned in the groups to their ongoing recovery. Consistent with a continuing care model, participants can attend as many MBRP sessions as they want to, and for as long as they want. Although the session content repeats every 8 weeks, we have found in our implementation of the program in community settings that individuals continue to attend beyond the full 8 sessions. Although themes are repeated, participants bring new experiences to the session, decreasing the risk of mere repetition. The group composition also includes people in various stages of recovery and familiarity with the material, which can make for richer discussions among group members themselves.

MBRP groups are facilitated by experienced community clinicians and clinical psychology graduate students. Facilitators were trained by SB and KW, who have trained MBRP facilitators for the past 2 decades. All MBRP facilitators are required to have a personal mindfulness practice and experience with mental health or addiction counseling. Many groups are cofacilitated with 2 or more facilitators and all facilitators receive group supervision from SB. The MBRP sessions are audio-recorded and uploaded to REDCap. Fidelity ratings of all group sessions are completed by a trained research coordinator and 10% of sessions are randomly selected for double coding by a trained graduate student or research assistant. Treatment fidelity is assessed using an adapted version of the Mindfulness-Based Relapse Prevention Adherence and Competence Scale (MBRP-AC) [65]. MBRP facilitators (n=15) are also invited to participate in the qualitative evaluation of the program.

To support group engagement and attendance, MBRP group attendees are provided weekly and monthly reminders of MBRP group times and any updates (eg, cancellations due to holidays). Groups are flexible, offered based on patient availability and interest such that new group times are formed to better accommodate participant schedules.

**Table 1. T1:** MBRP^a^ session content.

Session	Content
1	Eating meditation with a small piece of food (eg, dried fruit), introduction to the SOBER^b^ breathing space, and using mindfulness in daily life
2	Mindfulness of thinking and thoughts, breath meditation
3	Mindful movement, SOBER breathing space, mindfulness, and valued living
4	Body scan, developing a daily practice and common challenges therein, false refuge
5	Kindness practice
6	SOBER breathing space in a challenging situation
7	Mindfulness and acceptance of difficult emotions, the Guest House poem meditation, and reading
8	Urge surfing

a MBRP: mindfulness-based relapse prevention.

b SOBER: Stop-Observe-Breathe-Expand-Respond.

#### Referral to Online Mutual Support Condition

The orientation session for the referral group is the only intervention provided to the comparator group, consisting of an orientation to online mutual support programs: InTheRooms, AA online, and SMART Recovery. Referral sources for individuals who are in crisis (eg, calling 988) are offered, as well as information about optional mobile apps for those wanting mobile app support (eg, apps to track drinking).

Mutual support groups are free, peer-led organizations designed to help individuals with substance use disorders and other addiction-related problems. Mutual support groups often focus on communication and exchange of addiction and recovery experience and skills. Through shared activities and discussions, participants provide mutual support and learning among individuals facing similar challenges.

### Outcomes

#### Overview

All outcomes are assessed at each time point (baseline and at follow-up months: 6, 12, 18, 24, 30, and 36) and are studied over time with change from baseline to the last follow-up period as the analysis metric.

#### Primary Outcome

Given the focus of the interventions on continuing care for AUD, recovery from AUD was chosen as the primary outcome and is based on the most recent empirical definition of recovery developed by NIAAA [17]. This empirical definition of recovery is a binary (yes or no) outcome defined by achieving all three of the following: (1) remission from *DSM-5* AUD based on an 11-item AUD symptom checklist [66] (endorsing <2 criteria is AUD remission, excepting the craving criterion which may persist even during total abstinence); (2) cessation of heavy drinking (defined as not engaging in heavy drinking over the past 28 days with heavy drinking defined as 4 or more standard drinks per occasion for females, and 5 or more standard drinks per occasion for males, measured by the Timeline Followback [67]); and (3) improvements in functioning and well-being as measured by higher score (from baseline) on the World Health Organization (WHO) Quality of Life [68] domain scores (each of 26 items scored from 1 to 5 on a response scale, which are then transformed linearly to a 0‐100 scale) and the 36-item Short Form Health Survey (SF-36) [69] Mental Health Component Score (scored on a 0‐100 scale). Recovery is defined by the achievement of remission, cessation of heavy drinking, and improvements in functioning and well-being. The assessment of recovery is completed at all time points, with proportion change from baseline to the final follow-up period (3 years postbaseline) assessed as the primary outcome.

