Although effective pharmacological and psychosocial treatments for AUD exist [10], many individuals do not receive them and most are treated via mutual support group participation or community rehabilitation programs [11]. Approximately 80% of individuals with AUD never seek treatment, and not wanting to stop drinking is a common barrier to seeking treatment [9]. Many treatment programs in the United States are abstinence-based; yet, treatments that focus on reductions in drinking have been shown to be as effective in reducing alcohol-related harms [12]. Recent studies in population-based and clinical samples indicate significant health benefits from drinking reductions, without total abstinence [13-16]. Consistent with these data, the National Institute on Alcohol Abuse and Alcoholism (NIAAA) recently operationally defined recovery as remission from AUD, cessation of heavy drinking (defined as no more than 14 [males] or 10 [females] standard drinks per week and no more than 4 [males] or 3 [females] standard drinks on a single day), and improvements in functioning and well-being [17]. Following the *DSM-5* (*Diagnostic and Statistical Manual for Mental Disorders* [Fifth Edition]) definition, AUD in remission is classified as no longer meeting criteria for AUD (ie, 2 or more symptoms) [18]. Expanding the definition of recovery to include nonabstinent outcomes may increase provider awareness and acceptance of nonabstinent treatment goals; it may further increase treatment-seeking among those with AUD who are unwilling or unable to abstain but willing to reduce their drinking, and ultimately reduce the public health burden of untreated AUD [19,20].

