**Inclusion criteria**
At least 18 years oldReceived alcohol use disorder (AUD) treatment or made a self-change attempt to reduce or stop drinking in the past 3 months, or is interested in reducing or stopping drinkingMeet criteria for a current AUD, as defined by a score of 2 or greater on the Alcohol Symptom Checklist [60]Engaged in heavy drinking (more than 14 standard drinks per week or more than 4 drinks on a single day for men and more than 7 drinks per week or more than 3 drinks on a single day for women) in the past 6 monthsAble to understand all study procedures and able to consent in EnglishWilling to use a personal smartphone or tablet that is connected to the internet, or being willing to use a study-provided tabletHave access to a valid US mailing address for receiving the dried blood spot card and reside in the United States

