### Statistical Methods

#### Primary Outcome Analysis

We use a generalized linear mixed model (GLMM) that can accommodate a binary outcome (recovery vs not recovery as defined by the NIAAA definition [17]) and random effects that correct for the nonindependence of repeated measures in longitudinal data to assess within-person change over time. The recovery binary variable is created using the 3 indicators included in the definition at each time point. AUD remission is based on not endorsing criteria for AUD (other than craving which may persist even during abstinence), cessation of heavy drinking is defined by no self-reported heavy drinking days, and improvements in functioning and well-being as measured by higher score (from baseline) on the WHOQOL-BREF [68] domain scores (each of 26 items scored from 1 to 5 on a response scale, which are then transformed linearly to a 0‐100 scale) and the 36-item Short Form Health Survey [69] Mental Health Component Score (scored on a 0‐100 scale). The analyses consist of estimating a GLMM with fixed effects of baseline sociodemographics and covariates used in randomization (sex and AUD severity), fixed effects of random assignment to MBRP versus online mutual support referral, and random effects of time.

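### The primary outcome is labelled NIAAA-defined recovery, but its drinking component omits the weekly limit that the protocol itself gives as part of that definition

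*Protocol article*

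**What the plan says.** All references are to the protocol article.

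- **Background** describes NIAAA's cessation of heavy drinking as two limits that must both be met: "no more than 14 [males] or 10 [females] standard drinks per week and no more than 4 [males] or 3 [females] standard drinks" on any one day.
- **Eligibility Criteria (Textbox 1)** counts either kind of excess in the past 6 months as heavy drinking. The men's rule reads "more than 14 standard drinks per week or more than 4 drinks on a single day for men"; the women's has the same form, with 7 as the weekly figure and 3 as the daily one. Weekly volume alone is enough.
- **Primary Outcome** says that recovery "is based on the most recent empirical definition of recovery developed by NIAAA", citing the same reference as Background. Its drinking component is "not engaging in heavy drinking over the past 28 days" on the Timeline Followback, with "heavy drinking defined as 4 or more standard drinks per occasion for females, and 5 or more standard drinks per occasion for males". No weekly limit appears.
- **Primary Outcome Analysis** repeats the day-only rule ("cessation of heavy drinking is defined by no self-reported heavy drinking days") and describes the binary outcome as "recovery vs not recovery as defined by the NIAAA definition".

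**The concern.** The article states a two-part definition, cites it as the source of the primary outcome, and then scores one part. If the wording were only that the outcome is based on NIAAA's definition, an adaptation might be understood. The analysis section says that the outcome is as NIAAA defines it, and nowhere is a departure stated or justified.

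Two things are at stake. First, a reader of the results would take the drinking component to mean that both limits were respected, when only one was checked. Second, heavy drinking means different things at entry and at outcome. A participant who qualified on weekly volume alone, without ever passing the single-day limit, satisfies the outcome's drinking component at baseline and goes on satisfying it with no change in intake.

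**Working it through.** **The plan's own figures.** The article gives no figure for the effect of this choice. The nearest number is the power statement in Sample Size Considerations: Cohen h = 0.36, 215 per group, two-sided α = .05, power above .90. It reproduces: Φ(0.36 × √(215/2) − 1.96) = Φ(1.77) = 0.962. Its h comes from an earlier trial's result, so this calculation does not change with the point below.

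**Step 1: is the daily part the same everywhere?** In whole drinks, 5 or more (men) is the same as more than 4, and 4 or more (women) is the same as more than 3. Background, Textbox 1, Primary Outcome and the heavy-drinking-day definition under Reductions in Other Drinking Outcomes therefore agree on the day limit. Only the weekly part is lost.

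**Step 2: the largest intake that still scores as cessation.** Formula: (heavy-day threshold − 1) × 7.

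| | Most per day without a heavy day | Per week | Per 28 days | Ratio to Background weekly limit | Ratio to entry weekly limit |
|---|---|---|---|---|---|
| Men | 5 − 1 = 4 | 28 | 112 | 28/14 = 2.0 | 28/14 = 2.0 |
| Women | 4 − 1 = 3 | 21 | 84 | 21/10 = 2.1 | 21/7 = 3.0 |

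**Step 3: how often must someone drink at that level to pass the weekly limit?**

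- Men at 4 a day: 4 days a week (16 > 14).
- Women at 3 a day: 4 days a week against a limit of 10 (12 > 10), or 3 days a week against a limit of 7 (9 > 7).

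**Step 4: the protocol's own WHO risk bands.** These are in grams per day. The article gives no grams per standard drink, so the value is assumed and a range is shown.

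| Assumed g per drink | Men, 4 a day | Women, 3 a day |
|---|---|---|
| 14 | 56 g, moderate (41–60) | 42 g, high (41–60) |
| 13 | 52 g, moderate | 39 g, moderate (21–40) |
| 10 | 40 g, low (0–40) | 30 g, moderate |

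The women's band at the ceiling is high at 14 g and moderate at 13 g or 10 g, so no conclusion should rest on it.

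**Step 5: the women's weekly figure.** Background has 10 and Textbox 1 has 7. The two must be reconciled before a weekly limit can be scored.

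**The case against.** The strongest reply is that the scoring rule is explicit and applied consistently across the outcome and analysis sections, so nobody would be unsure how to compute it, and that only the label is at fault. Explicitness stands. It does not answer the mismatch, because the analysis section equates the rule with a definition that the article itself states differently.

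A reader might infer that people whose drinking has not changed would be reported as recovered. The documents do not support that. Recovery requires all three components. A participant must also have fewer than 2 AUD criteria, craving excepted, on a checklist covering the past 6 months at follow-up, and must have higher WHOQOL-BREF domain and SF-36 mental health scores than at baseline. What can be met without change is the drinking component, not the outcome.

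The figures of 28 and 21 are ceilings: they need the maximum permitted intake on every day and never one drink more. That is true, although Step 3 shows that the weekly limit is passed well short of daily drinking.

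It can also be said that volume is captured elsewhere, through the WHO risk-level reductions, drinks per drinking day, percent drinking days and PEth. These help interpretation but do not alter what the primary outcome counts. Entry and outcome thresholds need not be identical either. That is a fair point, but the mismatch with the cited definition remains without it.

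Finally, changing a primary endpoint after all 470 participants are randomized and 6-month data are in is not merely a scoring edit. This stands, and the fix allows for it.

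**Conclusion.** The point holds for the drinking component. The primary outcome carries the NIAAA label, but its scoring omits the weekly limit that the article presents as part of that definition. The omission allows up to 28 drinks a week for men and 21 for women, which is 2.0 times the weekly limit for men and 2.1 or 3.0 times for women, depending on which of the two stated figures applies. These results rest only on the article's thresholds and on counting in whole drinks. The comparison with the WHO bands needs the assumed grams per drink and is not relied on.

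The document does not say how many participants drink in this pattern or entered on weekly volume alone, so the effect on the recovery rate is unknown.

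A reader might also infer that the omission favours MBRP, because that arm supports reduction goals while the comparator includes referral to AA. The article gives no drinking patterns by arm, and the same rule applies to both, so no between-arm bias is shown.

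**What to change.** 1. Reconcile the women's weekly figure between Background (10) and Textbox 1 (7).
2. Before unblinding, amend Primary Outcome and Primary Outcome Analysis so that cessation means no day above the single-day limit and no week above the weekly limit of the cited definition, within the existing 28-day Timeline Followback window. State how the 28 days are divided into weeks.
3. Keep the day-only rule as a sensitivity analysis.
4. Report the change to the IRB, the DSMB and the trial registry, as the article requires for protocol modifications.

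If the day-only rule is to stay primary, state and justify the departure, stop describing the outcome as NIAAA-defined recovery, and prespecify the version with the weekly limit as a sensitivity analysis.

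**Cost.** No new data are needed, because daily drink counts are already collected. The timing is still workable: analysts are blinded, no interim analysis is planned, and the last participant was randomized on March 20, 2025, so 36-month follow-up runs to March 2028. The price is a documented amendment to the primary endpoint after randomization, and a recovery rate that can only stay the same or fall, by an amount that cannot be stated in advance.

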#### Secondary Outcomes: Mechanisms of Behavior Change

##### Overview

Several secondary outcomes are evaluated with the following measures completed at all time points (baseline 6, 12, 18, 24, 30, and 36 months), and the average change from baseline to the final follow-up period was assessed as the secondary outcome.

##### Reductions in WHO Risk Drinking Levels

The Timeline Followback [67] calendar method of assessing standard alcohol drinks consumed each day over the past month is used to calculate the WHO risk levels [70,71] based on sex-specific grams of alcohol consumed per day in the month prior to the assessment, with levels defined as low risk (0‐20 females or 0‐40 males), moderate risk (21‐40 females and 41‐60 males), high risk (41‐60 females and 61‐100 males), and very high risk (61+ female or 100+ males). We examine those who achieve at least a 1-level or at least a 2-level reduction in risk drinking levels. The reference group for the 1-level reduction is no change or increase in WHO risk drinking level and the reference group for the 2-level reduction is 1-level reduction, no change or increase in WHO risk drinking level.

##### Reductions in Other Drinking Outcomes

The Timeline Followback [67] calendar method of assessing standard alcohol drinks consumed each day over the past month is used to calculate reductions in several other drinking-related metrics. The Timeline Followback is administered by trained study staff via video call, entered into a visual calendar viewable by the participant, and then entered by trained staff into REDCap. Percent heavy drinking days is calculated as the number of heavy drinking days in the past month divided by the total number of days in that time period (typically 28 days, unless some days are missing), where heavy drinking is defined as 4 or more standard drinks for females and 5 or more standard drinks for males, and heavy drinking occasions are used to identify heavy drinking days. Drinks per drinking day is calculated using the total number of standard drinks consumed on each drinking day, and the number of standard drinks per drinking day is calculated as the total number of standard drinks consumed in the past month divided by the total number of days in that time period when drinking occurred. Percent drinking days is calculated as the number of drinking days in the past 90 days divided by the total number of days in that time period, with drinking occasions used to identify drinking days.

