MBRP facilitators are administered the MBRP self-report assessments listed in Table 3 above, including the Five Facet Mindfulness Questionnaire - Short Form, the Self-Compassion Scale - Short Form, the MBRP Practice Questionnaire, and the Applied Mindfulness Process Scale. MBRP facilitators also complete a measure of mindfulness meditation practice and retreat experience.

Process evaluation measures are guided by the RE-AIM (Reach, Effectiveness, Adoption, Implementation, Maintenance) model [90,91], which describes public health impact related to implementation research: (1) Reach: how many participants are impacted (eg, number of participants that engage in the MBRP program); (2) Effectiveness, such as rates of recovery and improvements in functioning among those who attend MBRP groups; (3) Adoption: continued engagement in offering the MBRP groups among the community clinician facilitators; (4) Implementation: extent to which the MBRP groups are attended and fidelity to the MBRP manual; and (5) Maintenance: the extent to which participants would continue attending MBRP groups and the extent to which community clinician facilitators would continue to offer the MBRP groups. We use a mixed methods framework. The quantitative metrics are gathered throughout the study. The qualitative interview guide is based on RE-AIM QUEST (Qualitative Evaluation for Systematic Translation) [90], tailored for MBRP. Qualitative interviews are conducted one-on-one with trained assessors via video calls. Facilitator participants and client participants are asked about their experiences with mindfulness generally, the THRIVE MBRP groups specifically, the THRIVE mobile app, and questions to assess potential facilitators and barriers to implementation of telehealth-delivered MBRP groups similar to those in THRIVE.

**Table 3. T3:** Constructs measured and specific assessments repeated every 6 months for 3 years.

Constructs	Assessment measures
Alcohol and drug use	Timeline Followback [67], alcohol and drug use past 6 months.
AUD^a^ severity	Alcohol Dependence Scale [92]
Diagnosis	*DSM-5^b^* AUD symptoms assessed by interview [93]
Alcohol problems	PROMIS^c^ alcohol consequences [75]
Craving	Penn Alcohol Craving Scale [79]
Psychosocial functioning	Psychosocial Functioning Inventory [94] WHOQOL-BREF^d^ [68] Purpose in Life [95]
Physical and mental health	PROMIS PROPr^e^ (functioning, sleep, pain, etc) [76], and PROMIS Meaning and Purpose measure [78]

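### Two Timeline Followback secondary outcomes are badly fixed: percent drinking days has conflicting windows, and the WHO level-reduction outcomes cannot be achieved from some baseline levels

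*Protocol article*

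**What the plan says.** **Window.** The section Reductions in Other Drinking Outcomes opens by saying that the Timeline Followback "calendar method of assessing standard alcohol drinks consumed each day over the past month is used to calculate reductions in several other drinking-related metrics". For percent heavy drinking days it gives the length of that period as "typically 28 days, unless some days are missing". Drinks per drinking day also uses the past month. Percent drinking days, in the same paragraph, does not: "Percent drinking days is calculated as the number of drinking days in the past 90 days divided by the total number of days". Table 3, under Data Collection and Management, lists the instrument as "Timeline Followback [67], alcohol and drug use past 6 months".

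**WHO levels.** The section Reductions in WHO Risk Drinking Levels defines four levels by average grams of alcohol per day in the month before assessment. Low risk runs from 0 to 20 g for females and 0 to 40 g for males, so abstinence is not a level of its own. Two binary outcomes follow: a reduction of at least one level and of at least two. For the first, the reference group "is no change or increase in WHO risk drinking level". For the second, a one-level reduction joins that reference group. Secondary Outcome Analyses fits a generalized linear mixed model to both outcomes. It states no restriction by baseline level, and the covariates it names are sociodemographics, sex and AUD severity.

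**The concern.** The secondary outcomes are changes from baseline, so the window decides what the baseline value means. Eligibility accepts a treatment episode or change attempt within the past 3 months. A 90-day baseline can therefore include drinking from before that attempt, which a 28-day baseline leaves out. Two analysts working from this text could build different variables under the same name.

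For the WHO outcomes, the number of levels a participant can drop is capped by where they start. Those who start at the bottom are counted as not achieving a reduction in either arm, whatever happens to them, including three years of abstinence. They add non-achievers to both arms and shrink the observed difference. What is at stake is sensitivity on two secondary outcomes and a clear reading of the reported proportions.

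**Working it through.** The article states no rate, sample size or power specific to these outcomes, so there is no figure to reproduce. The written definitions were applied directly.

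**1. Window**

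| Place | Window |
|---|---|
| Reductions in Other Drinking Outcomes, opening sentence | past month, typically 28 days |
| Same section, percent drinking days | 90 days |
| Table 3 | 6 months |

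If only 28 days are collected, a 90-day percentage cannot be formed. If 6 months are collected, it can, but then the past-month description is wrong and percent drinking days covers a different period from percent heavy drinking days and drinks per drinking day.

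The choice matters. Take a participant who drank daily until 28 days before baseline and then stopped:
- 28-day window: 0/28 = 0%.
- 90-day window: (90 − 28)/90 = 62/90 = 68.9%.

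If this person is still abstinent at month 36, the change from baseline is 0 points on one window and −68.9 points on the other.

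**2. Largest possible level reduction, by baseline level**

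| Baseline level | Largest drop | One-level outcome | Two-level outcome |
|---|---|---|---|
| Low | 0 | cannot be achieved | cannot be achieved |
| Moderate | 1 | possible | cannot be achieved |
| High | 2 | possible | possible |
| Very high | 3 | possible | possible |

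**3. Can low-risk participants enter?** The entry criterion is more than 14 drinks a week or more than 4 on one day for men, and more than 7 a week or more than 3 on one day for women, at any time in the past 6 months. Grams per day = drinks per week × grams per drink / 7. Grams per drink is an assumption: 14, with a range of 10 to 14.
- Man at 15 drinks a week: 15 × 14/7 = 30 g/day (range 21 to 30); low risk extends to 40.
- Woman at 8 drinks a week: 8 × 14/7 = 16 g/day (range 11 to 16); low risk extends to 20.
- One 5-drink day in 28 days and nothing else: 5 × 14/28 = 2.5 g/day (range 1.8 to 2.5).

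Heavy drinking earlier in the 6 months also qualifies, so the baseline month may contain little drinking or none.

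**4. Dilution of the one-level outcome.** Let s be the share at low risk at baseline. The observed proportions are p₁(1 − s) and p₂(1 − s), so the difference shrinks by the factor (1 − s). Assumed for illustration: p₁ = 0.65 and p₂ = 0.50 among those able to drop a level, 215 per arm (from Sample Size Considerations), two-sided α of .05, one time point, complete data. Power is from the normal approximation for two proportions, with pooled variance under the null.

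| s | Observed proportions | Difference | Power, all kept | Power, restricted |
|---|---|---|---|---|
| 0 | 0.650 vs 0.500 | 15.0 points | 0.885 | 0.885 |
| 0.1 | 0.585 vs 0.450 | 13.5 points | 0.80 | 0.85 |
| 0.2 | 0.520 vs 0.400 | 12.0 points | 0.71 | 0.81 |
| 0.3 | 0.455 vs 0.350 | 10.5 points | 0.60 | 0.75 |
| 0.4 | 0.390 vs 0.300 | 9.0 points | 0.50 | 0.69 |

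The restricted column uses 215(1 − s) per arm. For the two-level outcome, s becomes the share at low or moderate risk, which is at least as large.

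**The case against.** The percent drinking days formula is coherent in itself, since numerator and denominator refer to the same 90 days. A reader might infer that the value is impossible to compute, or that 28-day counts are set over 90, which would cap a daily drinker at 28/90 = 31.1%. The documents support neither reading: Table 3 has 6 months collected, and on that basis 90 days can be computed. What stands is the contradiction between the stated windows.

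The WHO outcomes are fully defined, and an unchanged level is an accurate description of someone who began and ended at low risk. Such participants are balanced between arms in expectation, so a claim of bias would be wrong. Eligibility shows that they can enter, not how many did; if few did, the dilution is trivial. Good status without a level change can also be captured by the recovery outcome and by percent heavy drinking days. All of this is fair, and it limits the point to lost power and a harder interpretation.

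A reader might also object that drinks per drinking day is 0/0 for an abstinent participant, and that multiple imputation would then give abstainers positive values. The arithmetic is right, but the scoring rule for zero drinking days is commonly left to the analysis plan, which is not shown. Nothing in Analysis Approach and Missing Data says that an observed month without drinking is treated as missing. That is not part of this point.

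**Conclusion.** Both parts hold in limited form. The window conflict is certain on the text and affects one named secondary outcome. The ceiling on WHO level reduction is also certain on the text. Its size depends on the baseline risk distribution, which the article does not give. At assumed low-risk shares of 20% to 40% and an assumed 65% against 50%, the difference falls from 15 points to between 12 and 9. Power is then about 0.71 to 0.50 with everyone kept, against 0.81 to 0.69 with restriction. The effect is dilution, not bias. The primary outcome uses its own 28-day definition of heavy drinking and is untouched.

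**What to change.** 1. Reconcile the Timeline Followback window across the two outcome sections and Table 3. State one window for percent drinking days, at baseline and every follow-up, preferably the 28 days used for percent heavy drinking days. If a longer calendar is collected, say so and say which part feeds each outcome. The cost is wording and scoring syntax; a 28-day measure is slightly noisier than a 90-day one.

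2. For the WHO outcomes, choose one of two routes:
   - Restrict the one-level outcome to participants at moderate risk or above at baseline, and the two-level outcome to those at high risk or above. Baseline level is fixed before treatment, so the randomized comparison is kept. The cost is a smaller analysis set and a narrower population.
   - Analyse the follow-up level as ordinal with baseline level as a covariate. This keeps everyone, but changes the estimand of a secondary outcome.

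In either case, report the baseline distribution of WHO levels by arm. The data needed are already collected, no interim analysis is planned, and analysts are blinded. The last participant was randomized in March 2025, so 36-month follow-up runs to about March 2028 and the change can be recorded before those data are complete.
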